### Randomisation and masking

Following study consent, eligible patients will be randomly assigned in a ratio of 1:1 to either complete the intervention survey or the control survey prior to surgery. Block randomisation will be performed by a computer-generated random assignment sequence prepared in advance. Opaque, numbered, tamperproof envelopes containing assignment will be prepared. Considerable effort will be made to avoid observer bias through separation of roles and blinding of trial staff. A research assistant independent of patient recruitment and data collection will be responsible for patient management. The research associate (who will be responsible for patient consent) will be blinded to group allocation. The surgeons involved in the consent of patients for TKA will have no role in the assignment process. Consenting surgeons will be blinded to patient allocation. In addition, outcome ascertainment will be blinded. Upon completion of the study, a biostatistician blinded to group allocation will analyse outcome data.

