## Methods

### Experimental design

The design is a two-arm, blinded, randomised controlled clinical trial comparing satisfaction and health outcomes of TKA patients who are provided with a DCE prior to undergoing TKA, with that of a control group. Patients in the intervention arm will complete a survey containing the DCE. Patients in the control arm will complete a survey that does not contain the DCE activity. Patients will also complete a brief patient expectation survey 1 week prior to scheduled TKA. Outcomes will be compared at 12 months after TKA. In addition, orthopaedic surgeons will complete a brief expectations survey for each patient consented for TKA. This will allow for a matched surgeon/patient comparison of expectations for recovery following TKA. The study strategy is registered, constructed and presented according to the recommendations of the Standard Protocol Items: Recommendations for Interventional Trials (SPIRIT) [25] (see Additional file 1 SPIRIT checklist) and Consolidated Standards of Reporting Trials (CONSORT) guidelines [26].

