### Intervention

Patients in the intervention arm will complete a survey containing the DCE. The DCE includes items about postoperative pain, stiffness, quality of life, complications and adverse events (health states) following knee replacement surgery. The remainder of the survey includes items about how much improvement in symptoms patients expect following knee surgery, the level of control, attitude towards taking risks, and the physical and emotional experiences associated with knee pain. Participants will be required to complete the survey prior to TKA during their routine preadmission appointment at SVHM. The survey will take approximately 30 min to complete. Patients will also be required to complete a brief patient expectation survey 1 week prior to scheduled TKA, which will take approximately 5 min to complete. Participants will complete the surveys electronically during their preadmission appointment. Surveys will be completed using a portable computer with administrative assistance provided from the study coordinator.

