### Timelines

This is a 1-year study with an anticipated start date of February 2016 and end date of January 2017. See Table 3 for SPIRIT schedule of study including enrolment, interventions and assessments.

**Table 3 Tab3:** SPIRIT trial study schedule

Activity/assessment	Enrolment	Randomisation	*t* _*1*_	*t* _*2*_	*t* _*3*_	*t* _*4*_
	−*t* _*1*_	0				
Baseline data, demographics	X					
Eligibility screen	X					
Informed consent	X					
Randomisation		X				
Baseline assessments battery^a^			X			
Expectation survey^b^				X		
Total knee arthroplasty					X	
12-month assessments^c^						X

^a^Baseline assessments will be given to patients during their preadmission appointments and completed with the assistance of the study coordinator. Assessment items include: Western Ontario and McMaster Universities (WOMAC) Osteoarthritis Index; Veterans RAND Health Survey mental component score (VR-12); Big Five Personality Inventory; Locus of Control; Risk Attitudes; Hospital for Special Surgery: Knee Surgery Expectations Survey; Fear Avoidance Beliefs Questionnaire; Pain Catastrophising Scale; Life Orientation Test-revised Questionnaire; and the DCE survey for patients in the intervention group

^b^Patients will complete the Hospital for Special Surgery: Knee Surgery Expectations Survey 1 week prior to scheduled TKA via phone with study coordinator

^c^12-month assessment will be given to patients at their 1-year post-TKA surgical review visit. Assessments include: WOMAC; VR-12 (this assessment is routine for all patients undergoing TKA)

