### Recruitment

Patients will be approached about participation in the study after consent for TKA, but before surgery. We chose to administer the DCE activity post consent for surgery so as to maintain surgeon blinding and avoid any influence the DCE activity may have on the consent process itself. It is possible but unlikely that completing the DCE activity may influence the decision to undergo TKA. Since we are using an intent-to-treat design, should this occur our statistical analyses will account for missing data by using multiple imputations. Potential patients waitlisted for TKA identified as meeting the inclusion criteria will receive both verbal and written information about the requirements for participation including: (1) verbal explanation of the project by the study coordinator upon initial contact during their attendance at the orthopaedic preadmission clinic at SVHM, (2) a detailed outline of the project content and required commitment in the Patient Information and Consent Form (see Additional file 2: Participant Information and Consent Form). Patients agreeing to take part in the trial will be required to provide written informed consent. Informed consent will be obtained by the research associate only after the patient has read and fully understands the details of the project.

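### The study coordinator both introduces the trial before consent and assists with a survey that reveals the arm, so under block randomisation the next allocation could be guessed better than chance

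*Protocol article*

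**What the plan says.** Under Randomisation and masking, the protocol article allocates patients 1:1 after study consent, using opaque numbered envelopes: "Block randomisation will be performed by a computer-generated random assignment sequence prepared in advance". The same section says "Considerable effort will be made to avoid observer bias through separation of roles and blinding of trial staff". It then names who is blinded: the research associate who takes consent, the consenting surgeons, outcome ascertainment and the biostatistician. The study coordinator is not on that list.

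Three other sections describe the coordinator's work:

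- Recruitment, before consent: "verbal explanation of the project by the study coordinator upon initial contact during their attendance at the orthopaedic preadmission clinic at SVHM".
- Intervention, after randomisation: "Surveys will be completed using a portable computer with administrative assistance provided from the study coordinator".
- Timelines, Table 3, footnote a: "Baseline assessments will be given to patients during their preadmission appointments and completed with the assistance of the study coordinator". The listed items end with "and the DCE survey for patients in the intervention group".

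Experimental design confirms that the two surveys differ visibly: "Patients in the control arm will complete a survey that does not contain the DCE activity".

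Outcome assessments (Data capture) adds that a study coordinator who does not know the arm will telephone patients who miss their review clinic at 12 months. Inclusion criteria limits the trial to one hospital.

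**The concern.** Opaque envelopes hide the next assignment. They do not hide what past assignments imply about it. In a blocked 1:1 list at one site, someone who has followed the earlier allocations can tell which arm is under-represented in the current block, and so which arm is more likely next.

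The coordinator role is placed to do this. It meets patients before consent, and at the same clinic appointment it later handles a survey that shows the arm. The article's main protection is separation of roles, and here two roles that should be apart are joined.

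At stake is whether the arms are comparable at entry. If expectations about the next arm influenced how or when the trial was put to a patient, the arms could differ in traits that affect WOMAC and satisfaction. Both are patient-reported, and blinded assessment at 12 months would not correct a difference that arose at entry.

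**Working it through.** **Inputs from the article.** 1:1 blocks, one hospital, list prepared in advance (Randomisation and masking; Inclusion criteria). The list has 132 allocations (Sample size).

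The 132 is used only as the length of the list, and it reproduces. For 77% against 51%, two-sided 0.05 and 80% power, the two-proportion formula gives 53 per group without continuity correction and 60 with it. Then 60 × 1.1 = 66 per arm, and 2 × 66 = 132.

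**Assumptions.** The article gives neither the block size nor whether it varies, so a range is used. The observer is assumed to have seen every earlier allocation in order and to guess the arm with more places left in the block. Both assumptions favour prediction, so the results are upper limits for each scheme.

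**Fixed, known block size B, with h = B/2.**

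- Certain in advance: allocations made after one arm is used up. The expected number of A's after the last B is h/(h+1), and the same holds with the arms exchanged. The expected count per block is therefore 2h/(h+1). Divided by 2h, the share is 1/(h+1) = 2/(B+2).
- Guessed correctly: expected count per block = h + ½[2^(2h)/C(2h,h) − 1], divided by 2h for the share.

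Example for B = 4: certain = 2/6 = 33.3%. Correct = [2 + ½(16/6 − 1)]/4 = 2.833/4 = 70.8%.

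| Block size | Certain | Of 132 | Guessed correctly |
|---|---|---|---|
| 2 | 50% | 66 | 75.0% |
| 4 | 33.3% | 44 | 70.8% |
| 6 | 25% | 33 | 68.3% |
| 8 | 20% | 26.4 | 66.6% |
| 12 | 14.3% | 18.9 | 64.3% |

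**Randomly mixed block sizes.** These were simulated with 500 lists of 132. The observer knows which sizes are possible but not their order, and updates after each allocation.

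| Sizes | Certain | Guessed correctly |
|---|---|---|
| 4/6 | 5.4% | 69.2% |
| 4/6/8 | 2.4% | 67.9% |

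As a check, the same simulation with fixed blocks of 4 gave 33.4% and 70.8%, in line with the formula.

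**Reading.** Mixing sizes removes most of the certainty (33.3% for fixed blocks of 4 falls to 5.4% for 4/6) but little of the advantage in guessing (70.8% to 69.2%). Keeping past allocations from whoever approaches patients brings the guess back to 50%, with none certain.

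**Passages side by side.** Recruitment places the coordinator before consent. Intervention and Table 3 place the same job title at the arm-revealing survey. Outcome assessments describes a coordinator as unaware of the arm at 12 months. If one person is meant, the last statement conflicts with the two before it. If several are meant, the article does not say which does what.

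**The case against.** The strongest reply is that the article nowhere says the coordinator chooses patients or tracks allocations. A reader might infer that one person decides whom to approach and knows every past assignment, and the text does not support going that far. Recruitment says that patients who meet the criteria are given information; it grants the coordinator no discretion over whom to approach. The help with the electronic survey is described as administrative, and there may be more than one coordinator. This stands. That the arm becomes visible is an inference, though a strong one, because only one survey contains the DCE.

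Second, a blinded research associate takes written consent, and randomisation follows. This stands as a real safeguard. It leaves only the manner and timing of the approach and explanation, which come before the associate's step.

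Third, a reader might conclude that 33 to 66 of the 132 allocations would be known with certainty. Those figures need a fixed block size that becomes known. An article may properly leave the block scheme to the full protocol, so its absence is no fault, and undisclosed varying sizes may already be planned. This stands against the certainty figures. It does not remove the better-than-chance guess, which persists in every scheme tried.

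Fourth, the arms differ by a questionnaire activity in a trial the article regards as low in risk, so the motive to steer is weak. WOMAC is analysed as change from baseline, psychological traits and comorbidity are recorded before surgery, and adjusted secondary analyses are planned. These are partial mitigations. The planned adjustment is for chance imbalances in measured characteristics, and it does not protect the main comparison.

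**Conclusion.** The overlap of roles is in the text, and it departs from the separation that the masking section promises. It also fits poorly with the blinded coordinator described for the 12-month calls.

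If the coordinator who introduces the trial sees past allocations, the next could be guessed correctly about 64% to 75% of the time with fixed, known blocks of 12 down to 2, and about 68% to 69% with mixed 4/6 or 4/6/8 blocks, against 50%. The share certain in advance ranges from about 2% to 50% over the assumed schemes. These figures assume full, ordered knowledge of earlier allocations.

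The documents do not show that selective recruitment would occur, and no size of bias can be derived from them. Bias in WOMAC change and satisfaction is possible, not established. The point is a cheap improvement of minor severity.

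**What to change.** - Recruitment: give first contact and the verbal explanation to the research associate, who is already blinded and already takes consent.
- Intervention and Table 3, footnote a: confine the coordinator who assists with the survey to tasks after randomisation. The associate should not be present while the survey is completed.
- Outcome assessments: state that a different, blinded person makes the 12-month calls.
- Randomisation and masking: add the coordinator to the account of who is and is not blinded. If this is not already so, use varying block sizes that are not disclosed to clinic staff. That measure alone is not enough, as the mixed-block results show.

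The cost is a swap of tasks between two existing roles and, at most, one changed setting when the list is generated. The small downside is that the associate must attend the preadmission clinic for first contact as well as consent. The article does not describe staffing, so the team should confirm that this is workable. No extra patients are needed.

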### Data management

All data will be stored on a password-protected computer kept in a secure locked facility and only accessible to the chief investigators and the trial coordinator as approved by the SVHM Human Research Ethics Committee (HREC). At the completion of the study, outcome data will be pooled and deidentified for analysis by a statistician. Due to the short duration and minimal risks of the trial, there will not be a data monitoring committee. However, the chief investigator will be responsible for overseeing the trial and ensuring data quality and completeness, including participant enrolment, consent eligibility and forms, allocation to study groups, data recording and timeliness of data collection. Furthermore, there will be no planned interim analyses and stopping guidelines.

### Statistical analysis

Statistical analysis will be by intention-to-treat. Categorical variables will be analysed using chi-squared tests (or Fisher’s exact test for small samples) while continuous variables will be analysed using *t* tests (parametric) and Mann-Whitney (non-parametric) tests for symmetrically and asymmetrically distributed data, respectively. The significance of differences in dichotomous data will be tested using generalised estimating equations or a linear mixed model. If there are chance imbalances in baseline patient characteristics hypothesised to influence the main outcomes, then statistical techniques that allow adjustment for confounding variables will be used as secondary analyses. DCE data will be analysed based on extensions to logistic regression, including multinomial logit models, mixed logit models and generalised multinomial logit models [45]. If there is more than 5 % missing data, sensitivity analysis allowing for different assumptions, such as the best or worst possible scenario, will also be reported for the main outcomes of the study. Cohen’s kappa coefficient will be used to assess concordance between surgeon and patient expectations.

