**Methods/design:**

One hundred and thirty-two people with end-stage OA on the waiting list for TKA will be recruited and randomly allocated to one of two groups using computer-generated block randomisation. A randomised controlled trial (RCT) adhering to SPIRIT and CONSORT guidelines will evaluate the effect of administering a DCE prior to surgery on patient-reported pain and function and satisfaction following TKA. Patients in the intervention arm will complete a survey containing the DCE, compared to the control group who will complete a modified survey that does not contain the DCE activity. The DCE contains information on actual risks of postoperative complications, as well as health status after TKA. The DCE encourages patients to actively make trade-offs between risks and health outcomes to elicit their preferences. Participants in both groups will be required to complete the survey after consenting to have the procedure, but prior to surgery during their routine preadmission appointment at St. Vincent’s Hospital, Melbourne, Australia (SVHM). Patients in both the intervention and control groups will also be required to complete a brief patient expectation survey 1 week prior to scheduled TKA. In addition, orthopaedic surgeons will complete a brief expectations survey for each patient consented for TKA to compare matched surgeon and patient expectations for recovery following TKA. Primary outcomes will be evaluated by a blinded examiner at 12 months post surgery using a validated self-reported pain and physical function scale, and a validated patient satisfaction scale. Secondary outcomes will include a range of validated measures of health and psychological wellbeing. All analyses will be conducted on an intention-to-treat basis using linear regression models.

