### Outcome assessments

#### Data capture

Demographic information collected at baseline will include age, gender, comorbidities, body mass index and socioeconomic data.

***Primary outcomes***: will be (1) changes in patient-reported knee pain and disability between baseline and 12 months post TKA, and (2) patient satisfaction.

Pain and physical function will be measured on the WOMAC Osteoarthritis Index [27]. The WOMAC consists of 24 items covering three subscales: pain (five items), stiffness (two items) and physical function (17 items). The pain and physical function subscales will be used, each subscale transformed to a score ranging from 0 to 100, with a higher score indicating greater pain and physical function. The WOMAC is a widely used questionnaire specifically designed to evaluate knee and hip OA [30, 31]. Patient satisfaction will be derived from the Self-administered Patient Satisfaction Scale (SAPS) for primary knee arthroplasty, a validated self-administered patient satisfaction scale [30]. Patients will be mailed both questionnaires at 12 months and patients who do not attend review clinics will complete the post-TKA surveys via phone call from a study coordinator, who will be blinded to intervention allocation.

***Secondary outcomes***: will be (1) changes in patient-reported psychological wellbeing between baseline and 12 months post TKA. Psychological wellbeing will be derived from the 12-item short form version of the Veterans RAND Health Survey mental component score (VR-12) [31], (2) differences in expectations of recovery between baseline and 1 week prior to scheduled TKA for patients in the intervention arm. Recovery expectations following TKA will be measured using the 19-item Hospital for Special Surgery: Knee Surgery Expectations Survey [32]. This measure forms a part of the larger study survey, but is measured before patients complete the DCE component, (3) concordance between matched surgeon and patient expectation for recovery following TKA. Surgeons will complete the same expectation survey as patients immediately following consultation and consent for surgery. The surgeon and patient expectation survey will then be paired for analysis.

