### Sample size

Intervention effectiveness will be evaluated by comparing change in the primary outcome measure between groups. We aim to detect minimum clinically important improvement (MCII) in the WOMAC. The sample size calculation was based on the following parameters: (1) an alpha value = 0.05, two-sided; (2) power = 80 %. To demonstrate a minimum clinically important difference in WOMAC scores of 15 points (SD [42]), between groups, the sample size required for each group is 45.

To demonstrate a difference in satisfaction the sample size calculation was based on the following parameters: (1) an alpha value = 0.05, two-sided; (2) power = 80 %; (3) expected rates of satisfaction at 1 year post TKA of 77 % for patients in the intervention arm prior to consenting to surgery compared to 51 % for patients undergoing standard procedural consent. The expected rates of satisfaction are derived from a recent study which reported 49 % of patients whose expectations were not met reported dissatisfaction with their TKA compared 6 % of patients whose expectations were met [13]. Incomplete data were reported in 17 % of the patient cohort and, therefore, these patients were not included in the analysis. We have, therefore, assumed a worst case scenario that these 17 % would have reported dissatisfaction despite having their expectations met. Based on these rates the sample size required in each group is 60. To allow for a 10 % dropout of patients, we will recruit 132 patients in total (66 per arm). This estimate is conservative based on our prior RCTs in TKA [43, 44], where we have achieved >95 % retention at 12 months.

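### The WOMAC change outcome gets an unadjusted t test or Mann-Whitney test; prespecified regression on baseline WOMAC would be more precise and would keep the mean difference as the target

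*Protocol article*

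**What the plan says.** The first primary outcome, under Outcome assessments (Data capture), is "changes in patient-reported knee pain and disability between baseline and 12 months post TKA". It is measured on the WOMAC pain and physical function subscales, each scaled 0 to 100. The Sample size section confirms the contrast: "Intervention effectiveness will be evaluated by comparing change in the primary outcome measure between groups".

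The Statistical analysis section gives one rule for continuous outcomes: "continuous variables will be analysed using *t* tests (parametric) and Mann-Whitney (non-parametric) tests for symmetrically and asymmetrically distributed data, respectively". No covariate appears in it. Adjustment is a separate, conditional step. Its sentence opens "If there are chance imbalances in baseline patient characteristics hypothesised to influence the main outcomes, then statistical techniques that allow adjustment", and the main clause gives the status of that adjustment: "statistical techniques that allow adjustment for confounding variables will be used as secondary analyses".

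Baseline WOMAC is in the assessment battery given at the preadmission appointment (Timelines, Table 3, footnote a).

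The Abstract (Methods/design) describes the analysis differently: "All analyses will be conducted on an intention-to-treat basis using linear regression models". It names no covariate, and the Statistical analysis section does not mention linear regression.

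**The concern.** There are two issues.

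- **Precision.** Subtracting baseline fixes the coefficient on baseline at 1. Regression of the 12-month score on arm and baseline estimates that coefficient, and in large samples its treatment estimate is never less precise. The protocol confines adjustment to secondary analyses and makes it depend on observed imbalance. That is a stated choice, not a detail left for later.
- **The quantity tested.** The test depends on the shape of the observed data. A t test addresses a mean difference, which is what the 15-point figure in the Sample size section describes. Mann-Whitney addresses whether patients in one arm tend to have larger changes than patients in the other. It corresponds to a mean difference only under a further assumption, such as a pure shift between arms. On that branch, the effect used for sizing is no longer what is tested, and the analysis is not the linear regression that the abstract announces.

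At stake are the width of the interval on a primary outcome and whether the primary effect measure is fixed before the data are seen.

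**Working it through.** **Inputs from the Sample size section:** two-sided alpha 0.05, power 80%, WOMAC difference 15 points, 45 per group for WOMAC, 60 per group for satisfaction, 66 per arm recruited to allow for 10% dropout. No numeric SD stands in the text.

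**Assumed, not in the document:** the correlation ρ between baseline and 12-month WOMAC (0.3 to 0.7), and the ratio k of the 12-month SD to the baseline SD (0.8 to 1.2).

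**Step 1: the plan's own figure.** Without an SD, 45 per group cannot be reproduced directly, so the SD is solved for. Normal approximation: SD = 15 × √(45/2) / (1.960 + 0.842) = 25.4. The two-sample t solution gives 25.1. Conversely, an SD of 25 gives 44 (normal) or 45 (t) per group. The figure is plausible with an SD of about 25, but the text does not say whether that SD is of change or of the 12-month score.

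**Step 2: relative variance.** In units of the baseline variance:

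- change score: k² + 1 − 2ρk
- regression on baseline: k²(1 − ρ²)
- difference: (1 − ρk)², which is never negative

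With k = 1 the ratio is (1 − ρ²) / [2(1 − ρ)] = (1 + ρ)/2.

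| ρ | k = 0.8 | k = 1 | k = 1.2 |
|---|---|---|---|
| 0.3 | 0.50 | 0.65 | 0.76 |
| 0.5 | 0.57 | 0.75 | 0.87 |
| 0.7 | 0.63 | 0.85 | 0.97 |

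The extremes: at ρ = 0.3 and k = 0.8, 0.5824/1.16 = 0.502, a cut of about 50%. At ρ = 0.7 and k = 1.2, 0.7344/0.76 = 0.966, a cut of about 3%.

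**Step 3: power at 60 per arm, 15-point difference, k = 1, normal approximation.** Power = Φ(15 / (SD × √(2/60)) − 1.96).

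*If 25.1 is the SD of change:* the standard error is 25.1 × 0.1826 = 4.58, and 15/4.58 − 1.96 = 1.31, so power is about 90.5% without adjustment. Regression multiplies the SD by √((1 + ρ)/2), which gives 98%, 97% and 94% at ρ = 0.3, 0.5 and 0.7.

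*If 25.1 is the SD of the 12-month score:* the SD of change is 25.1 × √(2(1 − ρ)) and the residual SD is 25.1 × √(1 − ρ²).

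| ρ | SD of change | Power, change | Residual SD | Power, regression |
|---|---|---|---|---|
| 0.3 | 29.7 | 79% | 23.9 | 93% |
| 0.5 | 25.1 | 90.5% | 21.7 | 97% |
| 0.7 | 19.4 | 99% | 17.9 | above 99% |

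**Step 4: abstract against methods.** Linear regression on arm alone is the equal-variance t test, so the abstract is compatible with the t-test branch. It cannot be read to include Mann-Whitney. The conflict is confined to that branch.

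**The case against.** The case for leaving the plan alone has real force.

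- **The comparison is valid.** An unadjusted comparison of change between randomised arms is unbiased. A reader might infer that the baseline is thrown away or that the result would be biased. Neither follows: the change score already uses the baseline, and its remaining correlation with baseline does not bias a randomised contrast. This stands.
- **The gain is uncertain.** The ratio (1 + ρ)/2 needs equal SDs, and the document gives neither ρ nor an SD. At ρ of 0.3 to 0.5 with equal SDs, the saving equals 33% to 54% more patients (1/0.75 and 1/0.65). A reader might take that as the size of the loss, but it is the favourable part of a range that falls to about 3% in variance. This also stands.
- **Satisfaction sets the sample size.** WOMAC needs 45 per group and satisfaction 60, so WOMAC has slack unless the implied SD refers to the 12-month score and ρ is low.
- **The primary covariates are not open.** A reader might infer that they wait on the data. They do not: the primary analysis has none, and imbalance-triggered adjustment is secondary and limited to characteristics thought to affect the outcome.
- **There are not two full rival primary analyses.** Step 4 shows that only the Mann-Whitney branch departs from the abstract.
- **The analyst is blinded to allocation** (Randomisation and masking). This limits steering of the test choice, but it does not settle which quantity is tested.
- **An article condenses the full plan,** and the rule for continuous variables is generic. But WOMAC change is continuous, no other rule is given for it, and adjustment is expressly made secondary. The point concerns what is stated, not what is absent.

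**Conclusion.** The point holds as one of efficiency and of a fixed effect measure, not of validity. The planned WOMAC comparison is unbiased but less precise than regression on a baseline score that the trial already collects. For assumed ρ of 0.3 to 0.7, the variance saving is 15% to 35% with equal SDs, and about 3% to 50% when the SD ratio may lie between 0.8 and 1.2.

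The consequence for power depends on what the implied SD of about 25 measures. If it is the SD of change, which fits the Sample size section's stated contrast, the trial is already well powered for WOMAC at 60 per arm and the benefit is mainly narrower intervals. A material power gain needs the other reading together with a low correlation.

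The Mann-Whitney branch is a separate defect that does not rest on these assumptions: it moves the test away from the mean difference used for sizing and disagrees with the abstract. The change is worth making because it is nearly free, not because the trial fails without it.

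**What to change.** Name as the primary analysis, separately for WOMAC pain and WOMAC function, a linear regression of the 12-month score on arm and the baseline score of the same subscale. Report the adjusted mean difference with its 95% confidence interval, whatever baseline imbalance or skew is observed. If residuals are skewed, use robust or bootstrap standard errors rather than a different test.

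Keep Mann-Whitney as a sensitivity analysis and any further covariate adjustment as secondary. Then make the Abstract and the Statistical analysis section name the same primary model; this also gives content to the abstract's reference to regression.

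The cost is a few lines of text. No additional patients, visits or data are needed.
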